Pulsed electromagnetic fields (PEMFs) might be classified as these treatments, because both anti-osteoporosis and anti-osteoarthritis effects have been reported respectively, but primarily with biomarker data [13–24]. No clinical research has ever been conducted to explore the anti-osteoporosis and anti-osteoarthritis effects of PEMFs simultaneously, especially using clinical data. In the clinical setting, the coexistence of postmenopausal osteoporosis (PMO) and lumbar OA is common, and if treatments could be applied to cope with these two problems at the same time, such a treatment would be significant. The primary goal of this randomized controlled trial (RCT) is to explore these two effects by treating PMO (diagnosed by evaluating BMD of proximal femur) with concomitant lumbar OA in southwest China.

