### Interventions

All included participants will receive conventional usual care (600 mg/day calcium and alfacalcidol vitamin D supplement 0.25 μg/bid) throughout the study period. Participants allocated to the PEMFs group will receive additional PEMFs treatment (40 min/treatment, 1 treatment session/day, 6 treatment sessions/week, for a total of 30 times as one course of treatment) for the first 5 weeks after enrollment, while those assigned to the sham PEMFs group will receive sham PEMFs treatment with the same device but no stimulus generated, indistinguishable from the real ones.

The PEMFs treatment will be applied using XT-2000B therapeutic stimulators (Tianjin xtmed, Tianjin, China) to generate time-varying fields consisting of bursts of asymmetric pulses. Each burst should last for 0.2 ms and repeat at a frequency of 8 Hz. The fields will be delivered perpendicular to the lumbar spine and proximal femur of the supine participant and the flux density within a single burst will start with a peak value of 3.82 mT and decrease to 0 mT in 0.2 ms.

All participants will be asked to refrain from seeking any other physiotherapy or medications throughout the study period, especially during the first 5 weeks after enrollment, when PEMFs are proposed to be delivered. Whereas afterwards, during the follow-up phase when all participants are scheduled to receive only usual care, the use of analgesia and non-steroidal anti-inflammatory drugs (NSAIDs) will be permitted for the sake of ethical considerations. However, the use of this sort of medications should not exceed 3 days in each week and should not occur within 48 h of a follow-up visit. Information regarding the types of treatments and corresponding consumptions will be collected at each visit, and comparability between groups will be tested using Mann-Whitney’s *U*-test.

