### Sample size

Because we could not identify data or citations proving references for the minimum clinically significant difference and corresponding standard deviation in proximal femur bone mineral density (BMDF) between the two arms, the “least detectable longitudinal change measured using dual-energy X-ray absorptiometry (DXA), that is, 0.023” was approximately used as the expected absolute intergroup difference and standard deviation [20, 27]. With a type I error probability of 5 % and a 90 % probability of avoiding a type II error, we would require 20 participants in each group. Assuming a loss to follow-up of 20 %, a total sample size of 50 participants (25 participants per group) is needed.

We did additional sample size calculation for pain intensity, the most important secondary endpoint, measured using the Visual Analogue Scale (VAS) on a scale of 0 to 100. With a standard deviation of 32.17 [28], type I error of 5 %, 90 % power, and a 20 % drop-out rate, approximately 25 patients would be needed in each group to show a minimum clinically significant difference, 30-points between groups [29].

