### Assessment

The primary outcome will be the mean percentage change in BMDF at 6-month follow-up. Proposed secondary outcomes were listed below: VAS; The mean percentage changes in bone mineral density of the lumbar spine (BMDL); serum 25-hydroxy-vitamin D (25(OH) D) concentrations; Oswestry Disability Index (ODI); manual muscle test (MMT) score; Berg Balance Scale (BBS) score; Timed Up and Go Test (TUG); hemorheological determinants; serum C-terminal telopeptide of type I collagen (sCTX I), serum bone alkalin phosphatase (sBALP), N-MID osteocalcin (N-MID); range of motion (ROM) of lumbar spine; overall functional ability using short form 36 item general health questionnaire (SF-36, Quality Metric, Inc., Lincoln, Rhode Island, USA); treatment compliance; health care consumption costs; possible adverse events (Additional file 1). Detailed information on some of the outcome measurements are described below:

As for BMD measurements, participants will be scanned in the standard manner by a technician using DXA (GE Lunar iDXA with encore 12.0 software, GE Healthcare Lunar, Madison, WI) following recommendations from the manufacturer. For proximal femur, BMD of the total hip will be recorded and analyzed, while for the lumbar spine the average BMD (aBMD) of the four vertebrae (L1-L4) will be extracted. All these data could be directly obtained using corresponding software without further calculations.

Manual muscle strength of the lumbar and the lower-extremity will be estimated by employing the MMT method with the traditional six-point ordinal Medical Research Council scale (0 to 5). Half-point scores will be used between all grades except that of 4 and 5, since it requires manual resistance that cannot be graded reliably [30]. All tests will be performed by a single examiner. Furthermore, before testing, the examiner and participants will all be required to rest for at least 5 min.

The BBS is a set that comprises 14 simple balance related tasks, ranging from standing up from a sitting position, to standing on one foot [31]. Another examiner will perform the tests for all the participants following the standard procedure. The examiner and participants will also be required to rest for at least 5 min before testing.

A TUG test will be conducted by recording the total time that a person takes to rise from a chair, walk 3 meters, turn around, walk back to the chair, and sit down [32]. It is intended to evaluate the functional mobility of the participants.

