We acknowledge limitations in the trial. First, the sample size calculation is somewhat imprecise, and there are many secondary outcomes, all at 0.05 significance in a trial with 25 subjects in each arm after accounting for a 20 % withdrawal. The risk of type I error may be very high. Second, the primary endpoint is BMDF, which is not as patient-relevant as fractures, so relevance of any positive result of this trial to patients needs further investigations in large well-designed trials. In spite of these limitations, our research also has strengths. One is that we refined our exclusion criteria to eliminate potential confounding factors as far as possible. We will exclude patients with confounding disorders and concomitant disorders that are of possibility to interfere with the balance of bone metabolism, and patients with lesions that may not be able to fulfill the study assessment. Furthermore, those who received treatments within 6 months before inclusion will also be excluded. Another one is the utilization of a patient-blinded design, with sham PEMFs arm to reduce the risk of bias. It is of great significance especially for the assessment of patient-reported outcomes (for example, pain), since without a proper patient-blinded design, identified differences could be interpreted as the results of placebo effect, which is found effective in the treatment of OA, especially for pain, stiffness and self-reported function [41]. There are other trials that have used sham PEMFs successfully. For example, Shi *et al*. evaluated outcomes of postoperative delayed union of long-bone fractures treated with an early application of PEMF, as compared with a sham-treated control group, where the coil was applied for 8 h/day with a sham signal generator from the same manufacturer [42]; Nelson *et al*. examined the pain-relieving effect of PEMFs and the sham devices they used were activated with a switch and had blinking indicator lights, just as active devices [43]. These two trials had used sham PEMFs successfully, and their findings were convincing.

In summary, this trial will provide preliminary evidence regarding the use of a nonpharmaceutical, noninvasive modality for managing PMO and lumbar OA. The success of this study will provide scientific evidence to primary care of postmenopausal women with these two common skeletal disorders.

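### Every analysis is judged at two-sided 0.05, and VAS pain, which carries most of the osteoarthritis half of the goal, has no named visit and no place in a testing order

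*Protocol article*

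**What the plan says.** **Goal.** The Background states: "The primary goal of this randomized controlled trial (RCT) is to explore these two effects", meaning the anti-osteoporosis and the anti-osteoarthritis effect. The Discussion calls the trial preliminary.

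**Primary outcome.** Assessment fixes one outcome at one visit: "The primary outcome will be the mean percentage change in BMDF at 6-month follow-up". The Primary analysis section agrees.

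**VAS.** The Sample size section makes "pain intensity, the most important secondary endpoint" the subject of a second calculation with 90% power. Assessment lists VAS first among the secondary outcomes, without a visit.

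**Analysis and threshold.** The Primary analysis section assesses treatment differences at three follow-up visits (5 weeks, 3 months, 6 months). The Secondary analyses section applies the same approach to the secondary outcomes. The last paragraph of the Health economics evaluation section sets two-sided P < 0.05 as the criterion for all the analyses. No order or adjustment is given.

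**Acknowledgement.** The Discussion lists as a limitation that "there are many secondary outcomes, all at 0.05 significance in a trial with 25 subjects in each arm" and says that the type I error risk may be very high.

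**Medication after week 5.** Interventions says that in the follow-up phase "the use of analgesia and non-steroidal anti-inflammatory drugs (NSAIDs) will be permitted". It limits use to 3 days a week and bars it within 48 hours of a visit. Consumption is recorded and compared between groups.

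**The concern.** The goal has two halves, and only one has a test with a fixed error rate. BMDF at 6 months cannot be changed once the data are seen. VAS can: as the article stands, a difference at any of three visits could be called significant and used to support an osteoarthritis effect, next to ODI, lumbar range of motion, SF-36 and other outcomes judged by the same threshold.

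This is more than an omission that an analysis plan might fill. The article states a decision rule, applies it to every analysis, and names its consequence without changing the rule. Acknowledging the risk does not reduce it while each P below 0.05 may still be called significant. At stake is what the trial may say about osteoarthritis, and so about both effects occurring together.

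**Working it through.** **1. The plan's own sample sizes** (Sample size section; 5% type I error, 90% power, 20% loss; z = 1.960 two-sided, 1.645 one-sided, 1.282 for power)

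BMDF, difference 0.023 and SD 0.023:
- n = 2 × (1.960 + 1.282)² × (0.023/0.023)² = 21.0, so 22 per group two-sided; one-sided gives 18. The stated 20 is within two of each.
- 20/0.8 = 25, as stated.
- Two-sided power with 20 per group: Φ(√10 − 1.960) = Φ(1.202) = 0.885 (t-test 0.869).

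VAS, difference 30 and SD 32.17, standardised difference 30/32.17 = 0.9325:
- Two-sided: n = 2 × (1.960 + 1.282)²/0.9325² = 24.2, so 25 per group before loss; 25/0.8 = 31.25, so 32 after it.
- One-sided: n = 2 × (1.645 + 1.282)²/0.9325² = 19.7, so 20; 20/0.8 = 25. The stated 25 including loss is reached only one-sided, whereas the article's rule is two-sided.
- Two-sided power with 20 evaluable per group: Φ(0.9325 × √10 − 1.960) = Φ(0.989) = 0.839 (t-test 0.820).

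**2. VAS claimable at any of three visits, no true effect**

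Independent visits: 1 − 0.95³ = 0.143. With correlated normal test statistics (simulated; the article gives no correlations, so these are assumptions):

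| Between-visit correlation | Chance of at least one P < 0.05 |
|---|---|
| 0 | 0.143 |
| 0.5 | 0.125 |
| 0.7 | 0.11 |
| 0.9 | 0.084 |

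**3. Secondary outcomes together**

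Assessment lists 16 items. Without compliance, costs and adverse events, 13 remain: VAS, BMDL, 25(OH)D, ODI, MMT, BBS, TUG, hemorheology, sCTX I, sBALP, N-MID, ROM and SF-36.

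- One treatment effect per outcome, independent: 1 − 0.95¹³ = 0.487.
- The same with an assumed between-outcome correlation of 0.3 (simulated): about 0.42.
- Upper count, each outcome tested separately at each visit (13 × 3 = 39), independent: 1 − 0.95³⁹ = 0.865. With assumed correlations of 0.3 to 0.7 between outcomes and 0.5 to 0.8 between visits, about 0.41 to 0.76.

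**4. Error of a dual-effect conclusion that requires both BMDF at 6 months and VAS**

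- BMDF has no effect: at most 0.05, because BMDF must be significant.
- BMDF works and VAS does not: up to 0.08 to 0.14 if any visit counts; at most 0.05 if one visit is fixed.
- In a fixed sequence, VAS is tested only after BMDF succeeds, so the chance of any false claim over the two tests stays at 0.05 without splitting alpha.
- Chance that both succeed with 20 evaluable per group, if independent: 0.885 × 0.839 = 0.74.

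**The case against.** The best defence is that this is a preliminary trial with a single primary outcome, properly fixed, and secondaries openly declared as unadjusted. Leaving secondaries unadjusted in such a trial is common. A visit and testing order for a secondary often sit in an analysis plan, and the visit schedule is in Additional file 1; neither is shown. Because the secondaries are to be analysed like the primary, VAS at 6 months is a natural reading. All this limits the point. It does not answer that the article applies one significance threshold to everything, and that no text shown fixes the visit of an endpoint given 90% power.

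Four stronger readings are tempting and not supported:

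- *The trial sets out to prove a dual effect.* The Background says the goal is to explore, and no section states a rule for declaring a dual effect.
- *The relevant error rate is 86%.* That needs 39 separate tests. The stated model (treatment fixed, time random, no interaction mentioned) can yield one treatment effect per outcome, hence 13 tests. Several outcomes may contain more than one variable, which would raise either count, but the article does not settle this.
- *A dual-effect conclusion has a 49% or higher error rate.* Those figures are for any one secondary being positive, which nowhere counts as success. Step 4 gives the relevant rates, which are much smaller.
- *Only the 5-week VAS is interpretable because analgesics are permitted afterwards.* The frequency limit, the 48-hour bar and the recording of use reduce the difference between visits, though they do not remove it. The Follow-up section includes the later visits to look for delayed effects. This bears on the choice of visit and does not decide it.

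**Conclusion.** The point holds in a limited form. The primary analysis is unaffected. The weakness is that a universal 0.05 rule, whose consequence the article itself concedes, covers a powered key secondary with no named visit. For VAS this means a false-positive rate of about 8 to 14% instead of 5%, if any of the three visits may be claimed and for between-visit correlations of 0.9 to 0. Across 13 secondaries with one test each, at least one false positive has a probability of about 49% if independent and about 42% at a correlation of 0.3. All correlations are assumptions. If VAS was always meant for 6 months, a sentence saying so removes the VAS inflation but leaves the threshold on the other secondaries. This should be corrected, because it determines what may be claimed about osteoarthritis.

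**What to change.** Trial status says recruitment is under way, so the change can be made before unblinding. Two statements suffice:

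1. Replace the universal threshold with a fixed sequence at two-sided 5%: BMDF percentage change at 6 months, then, only if that is significant, VAS at one visit named in advance. A dual-effect conclusion is supported only if both succeed.
2. Report all other outcomes and visits, including VAS at the remaining visits, as exploratory estimates with 95% confidence intervals and no significance claims.

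The sponsor should choose the VAS visit, weighing the post-week-5 analgesic allowance and its limits (Interventions) against the interest in delayed effects (Follow-up), and record the reason.

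Cost: none for the primary test. VAS becomes confirmatory only if BMDF succeeds, and the other secondaries can no longer be claimed as significant. The article should also state that two-sided VAS power with 20 evaluable per group is about 0.82 to 0.84, not 0.90; keeping 90% after 20% loss would take 32 per group.

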### Trial status

The trial is currently in the process of patient recruitment.

## Abbreviations

BBS: Berg balance scale
BMD: bone mineral density
BMDF: proximal femur bone mineral density
BMDL: bone mineral density of the lumbar spine
BMI: body mass index
DXA: dual-energy X-ray absorptiometry
ITT: intention-to-treat
LOCF: last observation carried forward
MMT: manual muscle test
N-MID: N-MID osteocalcin
NSAID: non-steroidal anti-inflammatory drug
OA: osteoarthritis
ODI: Oswestry disability index
PEMFs: pulsed electromagnetic fields
QALY: quality-adjusted life year
ROM: range of motion
sBALP: serum bone alkalin phosphatase
sCTX I: serum C-terminal telopeptide of type I collagen
SD: standard deviation
SF-36: Short Form 36-item General Health Questionnaire
TUG: Timed Up and Go test
VAS: visual analogue scale
25(OH) D: 25-hydroxy-vitamin D
